### Study design

The study is a combined multicenter randomized controlled trial (RCT) combined with an observational cohort study. Eleven centers in Australia will participate. The study Consolidated Standards of Reporting Trials (CONSORT) flowchart is provided in Fig. 1. The SPIRIT Checklist is provided in Additional file 1 and the Standard Protocol Items: Recommendations for Interventional Trials (SPIRIT) diagram is provided in Fig. 2

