### Recruitment

Patients will be approached on presentation to a participating institution either in the emergency department or in the outpatient setting. Patients aged 70 years and over with a displaced proximal humerus fracture with tuberosity involvement will undergo a computed tomography (CT) scan with 3D reconstructions to assess the fracture configuration and to assess the number of fracture parts according to Neer’s classification [6] (Table 1). Linear measurements will be made with digital calipers. The normal neck shaft angle will be assumed to be 130°. Verbal consent will be requested to allow questioning to assess eligibility and to collect identifiable data. The fracture type will be screened against the inclusion criteria by two of the principal investigators. Patients who satisfy the study criteria will be invited to participate in the study and will receive a Participant Information Sheet (see Additional file 1). Patients who are willing to participate in the randomized trial will be asked to sign a Consent Form. Basic demographic and radiographic data will be collected for both groups to assess independent variables (age, gender, fracture type, diabetes (yes/no), smoking status (current/non), baseline shoulder function (American Shoulder and Elbow Society (ASES) score, Disability of the Arm, Shoulder and Hand (DASH) score) and baseline health (EuroQol Health Survey 5 dimensions (EQ-5D) and EuroQol Visual Analog Scale (EQ-VAS)). Patients who are unwilling to participate in the randomized trial will be offered participation in the observational study and will be provided with a separate Participant Information Sheet and Consent Form.

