### Parallel observational cohort study

Patients who do not consent to be randomized will be offered participation in the observational arm of the study. Their treatment will consist of the same two treatment options as the RCT arm. Treatment will be decided by patient and surgeon preference as per usual practice at each institution. Treatment protocols, follow-up and outcome measures will be the same as the randomized arm. The outcome of this arm of the trial will be analyzed separately. The inclusion of the observational cohort will inform the generalizability of the randomized trial.

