#### Statistical analysis

Differences in baseline characteristics (i.e., intrinsic and injury-related variables) between both intervention groups will be assessed using the Student’ s *t* test (parametric continuous data), the Mann-Whitney *U* test (nonparametric continuous data) or the chi-square test (categorical data).

Unadjusted analysis by intention-to-treat will be performed to test the difference in primary and secondary outcomes between the intervention groups. Student’ s *t* test (parametric continuous data), the Mann-Whitney *U* test (nonparametric continuous data) or the chi-square analysis (categorical data) will be used. A *p* value < 0.05 (two-sided tests) will be taken as threshold of statistical significance.

The observational arm will be analyzed separately, comparing the same treatment groups against the same outcomes using multivariable linear regression to adjust for potential confounders (age, sex, handedness, smoking, fracture type).

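### The cohort regression leaves out baseline function, baseline health, diabetes and site, so measured confounding can remain in the non-randomised estimate

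*Protocol article*

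**What the plan says.** Four places in the protocol article bear on this.

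- **Statistical analysis** fixes both the method and the covariates for the observational arm. The same treatment groups are compared on the same outcomes, "using multivariable linear regression to adjust for potential confounders (age, sex, handedness, smoking, fracture type"). No other control for confounding is described.
- **Recruitment** states why baseline data are gathered: "Basic demographic and radiographic data will be collected for both groups to assess independent variables". The variables named are "age, gender, fracture type, diabetes (yes/no), smoking status (current/non), baseline shoulder function (American Shoulder and Elbow Society (ASES) score"), the DASH score, "and baseline health (EuroQol Health Survey 5 dimensions (EQ-5D) and EuroQol Visual Analog Scale (EQ-VAS").
- **Parallel observational cohort study** says how cohort patients come to their treatment: "Treatment will be decided by patient and surgeon preference as per usual practice at each institution". It also gives the cohort its purpose: "The inclusion of the observational cohort will inform the generalizability of the randomized trial".
- **Study design** gives the number of sites: "Eleven centers in Australia will participate". The Randomization section makes site a stratification factor in the trial.

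**The concern.** In the cohort nobody is randomised, so the comparison of surgery with nonoperative treatment depends on the adjustment. Prior shoulder function, general health and comorbidity can plausibly influence both the treatment chosen and the later ASES score. Baseline ASES is also the same instrument as the primary outcome. Local practice may shift treatment choice, and outcomes may differ between centres as well, since the Interventions section leaves approach, fixation and prosthesis to the surgeon.

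The plan names these variables as collected (site is known for every patient) and then fixes a model without them. If the cohort and trial effects turn out to differ, a real difference between populations could not be separated from confounding that the investigators had the data to reduce. That weakens the use for which the cohort was included.

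A smaller issue sits in the same sentence. Linear regression is named for all the outcomes, and these include complications such as dislocation, infection and death, as well as tuberosity healing, which are yes/no outcomes. The paragraph on the randomised arm separates continuous from categorical data, but the cohort sentence does not.

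**Working it through.** **Step 1: compare the two lists.** Inputs are the covariates in Statistical analysis and the baseline variables in Recruitment.

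| Variable | Baseline list | Cohort model |
|---|---|---|
| Age | yes | yes |
| Sex | yes | yes |
| Fracture type | yes | yes |
| Smoking | yes | yes |
| Diabetes | yes | no |
| Baseline ASES | yes | no |
| Baseline DASH | yes | no |
| Baseline EQ-5D | yes | no |
| Baseline EQ-VAS | yes | no |
| Handedness | no | yes |
| Site | no (known for every patient) | no |

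Nine variables are on the baseline list and five are in the model; four are common to both. So 9 − 4 = 5 listed variables are unused, and 5 − 4 = 1 model covariate (handedness) is not listed. Handedness appears nowhere else in the article text.

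**Step 2: can the omitted variables confound?** A confounder must relate both to treatment choice and to outcome. The cohort section bases choice on patient and surgeon preference within each institution's usual practice, so patient condition and site can both enter the decision. A link to later function is plausible for all the omitted variables. The documents give no data on the strength of either link.

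**Step 3: what size could it be?** The article states no cohort size, no baseline imbalance and no slope of follow-up ASES on baseline ASES. There is thus no planned figure to reproduce, and the bias cannot be calculated. The formula for one omitted covariate is

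bias = slope of the outcome on the covariate × difference in the covariate between treatment groups,

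with both terms taken after adjustment for the covariates already in the model. Slopes and imbalances below are **assumptions**; results are in ASES points.

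| Assumed slope | Imbalance 5 | Imbalance 10 | Imbalance 15 |
|---|---|---|---|
| 0.2 | 1.0 | 2.0 | 3.0 |
| 0.4 | 2.0 | 4.0 | 6.0 |
| 0.6 | 3.0 | 6.0 | 9.0 |

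For example, 0.4 × 10 = 4.0. The yardstick is the 10-point difference in Sample size calculation. The table shows only that the result depends on inputs nobody has yet; with no imbalance the bias from that covariate is zero.

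**The case against.** The strongest reply is that the mismatch between the lists shows a possibility, not a bias.

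- **Eligibility narrows the range.** Under Study population, everyone must be medically fit for surgery. Patients in residential aged care, with cognitive impairment, or with a prior condition severely affecting the shoulder are excluded. This stands: it limits differences in fitness and prior function, but does not remove them.
- **Direction is unknown.** A reader might infer that fitter patients choose surgery, so that the estimate leans toward surgery. The documents do not support this. Surgery could equally be chosen for worse injuries, and fracture type, which reflects injury severity, is already adjusted for. The article also does not say whether baseline ASES describes function before or after the fracture, so its prognostic slope is unknown.
- **The cohort keeps some value.** A reader might infer that it can no longer inform generalisability. That goes too far. With the same follow-up and outcomes, it still shows who declined randomisation, how they were treated and how they fared. The adjusted treatment contrast is what is weakened.
- **Handedness may be recorded anyway**, under basic demographic data. This is possible, so that part is only a mismatch to reconcile.
- **An analysis plan may say more.** This holds in part for the model form of each secondary outcome. It does not answer the covariate point, because the article itself states a specific list.
- **Cohort size is not given**, and complications may be rare, so a long covariate list could overfit. This stands and shapes the fix.

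**Conclusion.** The point holds in a limited form. The cohort model omits five variables that the article says are collected to serve as independent variables, and it omits site, while treatment follows preference and local practice. Measured confounding **can** therefore remain in the cohort estimate. Neither its size nor its direction can be derived from the documents; the 1 to 9 point range rests wholly on assumed slopes and imbalances and should not be cited as an expected bias.

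The conclusion assumes that the baseline scores are collected in the cohort as well as in the trial. The phrase about both groups in Recruitment could mean the two treatment groups or the two study arms. If the scores are not collected in the cohort, they have to be added there first.

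A reader might also infer that the main trial result is at risk, or that the randomised arm should be adjusted in the same way. Neither follows. The cohort is analysed separately, the randomised comparison is untouched, and whether to adjust it is a different question. The point deserves a correction, but it is not a threat to the trial's primary conclusion.

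**What to change.** In Statistical analysis, revise the cohort sentence as follows.

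1. Keep age, sex, smoking and fracture type. Add the baseline value of the outcome analysed (baseline ASES for the primary outcome), baseline EQ-5D or EQ-VAS, diabetes, and site as a fixed or random effect. If the cohort is small, put these variables into a propensity score instead.
2. Reconcile handedness with the baseline list: record it, or drop it from the model.
3. For complications and tuberosity healing, replace linear regression with a binary-outcome model, such as logistic regression, and use a reduced covariate set because events may be few.
4. State in Recruitment that the baseline scores are collected in the observational arm too.

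This is mainly a wording change using data already planned, plus one item on the baseline form if handedness is kept. Trial status says recruitment was not complete, so the change can be made before results are seen. The cost is a few more parameters and some loss of precision if the cohort is small. Confounding by unmeasured reasons for treatment choice will remain, and the report should say so.

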### Monitoring and quality assurance

Adverse events to be recorded are repeat shoulder surgery, readmission, infection requiring treatment, neurological deficit, dislocation and death. All adverse outcomes will be recorded centrally.

Data will be collected by local site investigators and study documents will be submitted securely (scanned and emailed) to the project manager at the administering institution. Identifying data will be transferred separately from any study information and stored separately to the study database. All research documentation will be labelled with a unique person number as an identifier and stripped of any potentially identifiable information. Data will be stored in password-protected computers and locked filing cabinets as required within the administering institution

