### Interventions

Participants who are randomized to surgery will be treated by insertion of a reverse total shoulder arthroplasty within 28 days of the date of injury. Surgical technique (approach, version, component fixation and prosthesis choice) will be left to the discretion of the treating surgeon. The glenosphere will be placed low, avoiding superior tilt. The tuberosities will be repaired using nonabsorbable sutures. Postoperatively, the arm will be placed in a shoulder immobilizer and patients will be instructed on elbow, wrist and hand exercises to commence immediately. Two weeks postoperatively, pendular exercises and passive flexion to 90° and passive external rotation to neutral will be commenced. Unrestricted passive and active assisted exercises will be allowed, graduating to active mobilization (as tolerated) at 6 weeks post surgery. Resisted range of motion exercises will be allowed after 12 weeks. A minimum of five physiotherapy contacts within 3 months of treatment will be provided.

Patients randomized to nonoperative treatment will be placed in a shoulder immobilizer. Elbow wrist and hand exercises will be allowed immediately. After 2 weeks, pendular exercises and passive flexion to 90° and passive external rotation to neutral will be commenced. Unrestricted passive and active assisted exercises will be allowed graduating to active mobilization (as tolerated) at 6 weeks. Resisted range of motion exercises will be allowed after 12 weeks. A minimum of five physiotherapy contacts within 3 months of treatment will be provided.

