### Outcome measures

Participants will be followed up at 6 weeks, 3 months, 6 months, 1 year, 2 years, 5 years and 10 years. The outcome measures listed below will be assessed at 6 weeks, 3 months, 6 months, 1 year, 2 years, 5 years and 10 years.

The primary outcome will be the ASES (American Shoulder and Elbow Society) standardized shoulder assessment score patient self-reported section at 24 months [27]. This scoring system consists of two dimensions: pain and activities of daily living, which are both equally weighted giving a total score out of 100, with higher scores indicating less pain and better function. It has been shown to be reliable, valid and responsive in shoulder arthroplasty and fracture [28, 29]. Secondary outcome measures will include DASH (Disability of the Arm, Shoulder and Hand) score [30], the EQ-5D and the EQ-VAS, pain (verbal numerical rating scale, 0–10 points), radiological parameters and complications (repeat shoulder surgery, readmission, infection requiring treatment, neurological deficit, dislocation, death). Radiographs will be performed at each follow-up and will include a four-radiograph series: an AP view in neutral and 30° external rotation, and a transthoracic scapula “Y” view and axillary view. Radiographic parameters that will be assessed are: healing of the tuberosities (nonunion or resorption will be considered failures to heal), position of the tuberosities, scapula notching (according to the Sirveaux classification system [31]) and loosening and alignment (coronal and sagittal plane for patients treated nonoperatively). All radiographs will be assessed by two independent observers independently. In case of discrepancy the scoring will be decided by discussion.

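### The complications outcome is not arm-neutral: read literally, 'repeat shoulder surgery' leaves out a first operation after failed nonoperative treatment

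*Protocol article*

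**What the plan says.** Monitoring and quality assurance gives the list: "Adverse events to be recorded are repeat shoulder surgery, readmission, infection requiring treatment, neurological deficit, dislocation and death". The next sentence adds: "All adverse outcomes will be recorded centrally". Outcome measures repeats the six events as a secondary outcome: "complications (repeat shoulder surgery, readmission, infection requiring treatment, neurological deficit, dislocation, death".

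Statistical analysis then has the secondary outcomes compared between the randomized groups without adjustment, by intention-to-treat, using a chi-square test for categorical data. The list therefore defines an endpoint that is tested between arms as well as what is monitored.

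On the two treatments, Interventions gives one arm a reverse total shoulder arthroplasty. For the other it says: "Patients randomized to nonoperative treatment will be placed in a shoulder immobilizer", followed by exercises and physiotherapy. On setting, Recruitment says: "Patients will be approached on presentation to a participating institution either in the emergency department or in the outpatient setting". The article does not say whether nonoperative patients are admitted.

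**The concern.** Two of the six terms are defined relative to something that has already happened. *Repeat* surgery needs an earlier operation, and *re*admission needs an earlier admission. The arthroplasty arm has both by design. The nonoperative arm has no index operation, and the article states no index admission for it.

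Surgery on a shoulder that has done badly without an operation is an obvious failure event for the nonoperative arm. If the definition passes over it while counting revisions after arthroplasty, the comparison of complications makes surgery look worse than it is. The article's own case rests on weighing benefit against harm: under Sample size calculation it sets the target difference at what would justify the added costs and risks of surgery.

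The wording also leaves room for sites to differ. Eleven centers collect the data, and the investigators and surgeons know the allocation. One site may count a first operation as an event and another may not.

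**Working it through.** No figure in the article depends on this definition, so there is no stated number to reproduce. The check is a reading of the sections together, followed by an illustration.

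**Step 1: apply the terms to each arm.**

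| Event | Arthroplasty arm | Nonoperative arm |
|---|---|---|
| Further surgery after the index arthroplasty | Counted as repeat surgery | Not applicable |
| First shoulder operation after failed nonoperative treatment | Not applicable | Not repeat surgery, so not counted under that term |
| Later admission, patient admitted at the outset | Counted as readmission | Counted as readmission |
| Later admission, patient not admitted at the outset | Does not arise (the index operation is taken to involve an admission) | Not a readmission, so not counted |
| Infection requiring treatment, neurological deficit, dislocation, death | Counted | Counted |

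The imbalance lies in the surgery term for the whole nonoperative arm, and in the admission term for those of its patients not admitted at the start. The other four terms can apply in either arm.

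**Step 2: direction.** Let r be the proportion of the arthroplasty arm with further shoulder surgery and d the proportion of the nonoperative arm with a first shoulder operation. Ignore second operations in the nonoperative arm. The difference, arthroplasty minus nonoperative, is:

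- literal wording: r − 0 = r
- arm-neutral wording: r − d
- bias of the literal wording: r − (r − d) = d, always against surgery

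**Step 3: size, under assumed rates only.** The target of 72 patients gives 72 / 2 = 36 per arm. The documents give neither r nor d. Taking r from 2 to 10% and d from 5 to 20%:

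| r | d | Expected patients (36r v 36d) | Literal difference | Arm-neutral difference |
|---|---|---|---|---|
| 2% | 5% | 0.7 v 1.8 | +2 points | −3 points |
| 2% | 20% | 0.7 v 7.2 | +2 points | −18 points |
| 5% | 10% | 1.8 v 3.6 | +5 points | −5 points |
| 10% | 5% | 3.6 v 1.8 | +10 points | +5 points |
| 10% | 20% | 3.6 v 7.2 | +10 points | −10 points |

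The literal wording gives +2 to +10 points. Arm-neutral wording gives +5 to −18 points. The sign changes whenever d exceeds r.

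**Step 4: what this does to a test.** Suppose there are 2 revisions after arthroplasty and 4 first operations in the nonoperative arm, again assumed. For counts a and c out of 36 each, the uncorrected chi-square is 72 × [a(36 − c) − c(36 − a)]² / [(a + c)(72 − a − c) × 36 × 36].

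- Literal, 2 v 0: 72 × 72² / (2 × 70 × 1296) = 2.06, p about 0.15.
- Arm-neutral, 2 v 4: 72 × (−72)² / (6 × 66 × 1296) = 0.73, p about 0.39.

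Neither is significant. In this example the reported direction changes, but the result of the test does not.

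**The case against.** The strongest reply is that the plan does capture nonoperative failure. Radiographs at each follow-up assess "healing of the tuberosities (nonunion or resorption will be considered failures to heal), position of the tuberosities" and also "loosening and alignment (coronal and sagittal plane for patients treated nonoperatively". The ASES, DASH, EQ-5D, EQ-VAS and pain scores are collected in both arms. A reader might infer from the complication list that failed nonoperative treatment goes unrecorded; the documents do not support that. What remains is narrower: none of these measures counts an operation.

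The sentence on central recording of all adverse outcomes may be read as widening the list, or only as saying where the listed events are held. It therefore does not show that the list is closed. Even on the wider reading, it does not change how the compared outcome is defined under Outcome measures.

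A reader might also infer that a nonoperative patient cannot be readmitted. Recruitment says where patients are approached, not where they are managed, and some may be admitted. The point about admission is therefore conditional.

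A further tempting reading is that non-fatal medical or intraoperative events during the surgical stay are missed. General recording of serious adverse events is something a condensed article may leave to the full protocol, so its absence here is no evidence of a gap.

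Finally, sites may already take 'repeat' loosely. If so, the change only writes down what is meant. The point itself is not one of condensation: the list is stated twice with the same terms, and the problem is what those terms say.

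**Conclusion.** The point holds for the surgery term, and for the admission term in any nonoperative patient not admitted at the outset. Read literally, the definition omits a first shoulder operation in the nonoperative arm while counting a revision in the other, which biases this secondary comparison against surgery. The bias in the surgery term equals the rate of first surgery in the nonoperative arm. The documents do not allow that rate to be computed; the 5 to 20% used above is an assumption.

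A reader might go further and conclude that the trial's benefit-risk judgement cannot be trusted. That does not follow. The defect touches two of six terms in a secondary outcome. The trial is sized on ASES alone, and neither the primary outcome, its analysis nor the sample size depends on the complication list. The conclusion rests on a literal reading of 'repeat' and 'readmission', which a fuller protocol might define differently.

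**What to change.** Make the same change under Outcome measures and under Monitoring and quality assurance:

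- Replace the surgery term with: *any surgery on the study shoulder other than the allocated index procedure, including first surgery after nonoperative treatment*.
- Replace the admission term with: *any unplanned hospital admission after the initial treatment episode*.
- Keep infection requiring treatment, neurological deficit, dislocation and death as listed, and compare all six between arms. Restricting the comparison to the reworded items could drop harms such as dislocation, and the Background names instability as a reported complication of reverse arthroplasty.

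The observational cohort uses the same outcome measures, so the new wording should apply there too.

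The cost is a small change to the case report form and slightly more event recording at sites. Recruitment was still open when the article was written and follow-up runs to 10 years, so the change is feasible.
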